##### Primary outcome

The primary outcome will be the change in the Alcohol Use Disorders Identification Test (AUDIT [6]) score between the 6-month follow-up and baseline assessments. The AUDIT is a 10-item self-report measure designed to assess alcohol misuse. Overall, the measure provides an indication of both alcohol use and alcohol-related problems. The AUDIT is a widely used, reliable, and validated estimate of alcohol misuse [6].

##### Secondary outcomes

Secondary outcomes include:
The self-reported number of (Estonian) standard drinks and alcohol-free days on a typical week over the past 6 months. This measure has been selected for use to allow for comparisons with results from an ongoing study being spear-headed by the World Health Organization [18].Drinking motives are being measured using the Drinking Motives Questionnaire (DMQ-R-5). The DMQ-R measures how people score on four motivational dimensions. Originally developed by Cooper [19], the underlying factor structure was confirmed by Kuntsche et al. [20] in Switzerland. The four motive types are social (e.g., drinking to be sociable, to celebrate, at parties); coping (e.g., drinking because it makes you forget about problems); enhancement (e.g., drinking to feel better or to be able to do things otherwise impossible); and social pressure and conformity (e.g., drinking because others do, to fit in).Motivation for Change (3 items). Participants rate how *important*, how *confident* and how *ready* they are to change their alcohol use, on scales from 0 to 10.Mental health is being measured with the 5-item version of the Mental Health Inventory [21]. The MHI-5 is about recent mental distress and a self-reported diagnosis of depression. It is well validated and easy to use.Treatment retention is defined as the percentage of data fields filled out in the weekly alcohol consumption diary over the 8 weeks of the intervention.Further illicit drug consumption is being accounted for via the NIDA-Modified ASSIST questionnaire [22].The “Customer Satisfaction Questionnaire” for internet interventions (iCSQ-8 [23]) is being used to assess satisfaction with the program in the intervention group. The iCSQ-8 has been extensively studied and results in scores from 8 to 32 (higher = better). We will implement a slightly-adapted version to account for Estonian practices.To check if participants used the resources provided by the program (treatment group only) and/or if they used additional resources (both groups) to treat themselves for their alcohol use, they are asked how many hours they invested in such material. Moreover, they are asked whether they employed professional help (consultation) to reduce their alcohol use (GP, psychologist, psychiatrist, other health specialist); and, if so, how many hours.

### Sample size calculation

A recent meta-analysis [24] showed that combining CBT and MI resulted in statistically-significant reductions in alcohol use, with effect sizes in the small range for internet interventions (*g* = .20). As we aim to compare the *“Selge” program* with a control condition which provides extensive resources and a self-administered test of alcohol abuse, we expect larger effects. The study that comes closest to our design compared online Personalized Normative Feedback (PNF) plus an intensive, but unguided CBT (56 daily sessions plus six weekly follow up sessions) program versus PNF with an online booklet; it also recruited alcohol misusers from the general population and it generated a Cohens’ *d* = 0.20 [11]. As we are offering a minimal-guidance intervention and comparing it to a self-administered test with routine advice on usual treatment, we expect a Cohens’ *d* = 0.23 for the current study. Using G*Power, the sample size required to detect this small effect with 80% power and α = 0.05 is *N* = 596 total (298 per group).

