### Randomization and trial flow

The baseline assessment starts with a suicidality screener [13]. Users indicating a higher risk of suicidality are excluded from the study and program and provided with a list of help lines. Users who do not meet the requirements for AUDIT are excluded from the study, but remain free to use the program, nevertheless. Users who fulfill the requirements after the baseline assessment are considered study participants and randomly assigned by a simple server randomization in a 1:1 ratio to either the *“Selge” program* or the control condition (see Fig. 2), informed about their assignment, and given further instructions. Participants in the control group are informed that they can use the program after 6 months, and provided with a help page — “Where to turn” — which is described in detail later in this paper. After 8 weeks (end of treatment), both groups undergo an assessment, as well as 6 months after baseline. An email prompt is sent automatically for each assessment, followed by two additional reminders sent to those who still have not completed the assessment. The last reminder sends a system email to the non-blinded study coordinator who then tries to contact the participant by phone up to twice. Participants are not compensated for completing the follow-up assessments. However, from all participants who complete all assessments, ten will be randomly selected to win a smartphone.

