### Data analysis plan

All analyses will be guided by the intention to treat (ITT) principle. Preliminary testing will assess two things: differences between the two study arms at baseline; and the degree of missing data. Baseline differences will be analysed by (generalised) linear mixed models (LMM). Missing data will be addressed by multiple imputation procedures from Amelia II through R [25]. Imputed data will be analysed with multinomial and binary regression models, considering two-sided tests with a type I error rate of *p* < 0.05 as statistically significant. Results will be cross-checked with complete case analyses of non-imputed data. Besides ITT analyses, we will also perform per-protocol analyses.

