We chose not to limit our program to harmful and hazardous alcohol users only (AUDIT scores ≥8 and < 20), but also to include alcohol users suggestive of dependence for two reasons. First, we did not want to limit access to the intervention since this is the first program in Estonia of its kind and treatment coverage remains low [5]. Second, we wanted to allow for comparison of our results against other studies, like the one spear-headed by the World Health Organization (WHO) [18].

We have decided to conduct both a post-intervention measurement and a follow-up measurement in order to distinguish the intervention effects from any follow-up effects. However, this can reduce the post-intervention and follow-up survey rates, especially since it is an internet intervention. To minimize the risk of excessive loss to follow-up, we have integrated into our design additional telephone calls. We therefore expect follow-up rates of 50–70% at post-intervention and 40–60% at 6 months follow-up [10, 12].

As with every internet-based program for the reduction of alcohol use, we expect a comparatively-high rate of dropout. However, due to the central implementation of the program in Estonians’ alcohol intervention efforts, its uniqueness in Estonia, and its cultural adaptations which include videos in each module, we expect that treatment adherence will be relatively high and the dropout rate relatively low.

Primary trial findings will be published in open-access journals, so both the public and policymakers in Estonia can learn about the intervention and the study results on 2020. Participant-friendly summaries of trial findings will be published on the program website.

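### The stated 80% power holds only if all 596 participants give a 6-month AUDIT score, while the protocol itself expects 40–60% follow-up at that point

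*Protocol article*

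**What the plan says.** Under Sample size calculation, the protocol article plans for a Cohen's d of 0.23 and reports "the sample size required to detect this small effect with 80% power". The requirement is given "with 80% power and α = 0.05 is *N* = 596 total (298 per group"). No allowance for loss to follow-up is mentioned. The Abstract sets the number to be recruited and randomised at 600. Allocation is equal: participants are "randomly assigned by a simple server randomization in a 1:1 ratio". The Data analysis plan specifies the tests by "considering two-sided tests with a type I error rate of" 0.05, handles missing data by multiple imputation and cross-checks against complete cases. The Abstract names (generalised) linear mixed models.

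Under Primary outcome, the endpoint is the change in AUDIT between baseline and 6 months. The Discussion, after mentioning the added telephone calls, says: "We therefore expect follow-up rates of 50–70% at post-intervention and 40–60% at 6 months follow-up".

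On the planning effect, Sample size calculation cites d = 0.20 from the study closest in design. It also says of a control condition "which provides extensive resources and a self-administered test of alcohol abuse, we expect larger effects". A later sentence in the same section gives a different reason for 0.23: the intervention has minimal guidance and is compared with a self-test plus routine advice.

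**The concern.** The article gives the number of outcomes needed for 80% power and, separately, the share of outcomes it expects to obtain. Put together, they do not deliver 80%. The calculation treats everyone randomised as measured at 6 months, whereas the Discussion expects 240 to 360 of 600. This is not a detail left to a fuller document, because both figures stand in the article.

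The Discussion ties future advertising and implementation of the program to whether it turns out to be effective. If the trial has roughly even odds of detecting its own assumed effect, a non-significant result says little about whether the program works. A reader relying on the stated 80% could give such a result more weight than it can bear.

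**Working it through.** **Inputs from the article.** d = 0.23, α = 0.05, 80% power, N = 596 (Sample size calculation); two-sided tests (Data analysis plan); 1:1 allocation (Randomization and trial flow); 600 randomised (Abstract); 6-month follow-up 40–60% and 8-week follow-up 50–70% (Discussion).

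**Step 1: reproduce 596.** For a two-sample t-test with n per arm, the noncentrality is d√(n/2) on 2n − 2 degrees of freedom. Solving for 80% power at d = 0.23, two-sided 0.05, gives n = 297.7, rounded up to 298 per arm, 596 in total (power 0.800). A one-sided test would need about 234 per arm and does not match. So 596 is the fully observed requirement with no attrition term.

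**Step 2: apply the expected follow-up.** Observed n per arm = 300 × follow-up. Power uses the same noncentral t at d = 0.23; the last column solves for the d that gives 80% power.

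| 6-month follow-up | Observed per arm | Power at d = 0.23 | d detectable with 80% power |
|---|---|---|---|
| 100% | 300 | 0.80 | 0.23 |
| 60% | 180 | 0.59 | 0.30 |
| 50% | 150 | 0.51 | 0.32 |
| 40% | 120 | 0.43 | 0.36 |

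**Step 3: number randomised that would yield 596 observed.** 596 / 0.60 = 993.3, so 994; 596 / 0.50 = 1192; 596 / 0.40 = 1490.

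**Step 4: what imputation can recover from the 8-week AUDIT (T1).** Assume monotone dropout, T1 follow-up 10 points above 6-month (T2) follow-up, and a T1–T2 correlation ρ of 0.6–0.8. The article gives no correlation. The effective n per arm is n₂ / [1 − ρ²(1 − f₂/f₁)], where n₂ is the number observed at T2 and f₁, f₂ are the follow-up fractions.
- 50% / 40%, ρ = 0.6: 120 / (1 − 0.36 × 0.2) = 129.3, power 0.45.
- 70% / 60%, ρ = 0.8: 180 / (1 − 0.64 × 0.143) = 198.1, power 0.63.

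**Step 5: what adjustment for baseline AUDIT could recover.** Assume d is scaled on the raw 6-month SD and the baseline to 6-month correlation is r. The effective n is n / (1 − r²).
- r = 0.5: 120 / 0.75 = 160, power 0.54; 180 / 0.75 = 240, power 0.71.
- r = 0.65: 120 / 0.5775 = 207.8, power 0.65; 180 / 0.5775 = 311.7, power 0.82.
- The r needed for 0.80 is √(1 − n/297.7): 0.63 at 60% follow-up, 0.70 at 50% and 0.77 at 40%.

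If d is instead scaled on the change-score SD, the effective n is n / [(1 + r)/2]. At r = 0.5 the result is the same as above; at r = 0.65 it is 145.5 to 218.2, giving power 0.50–0.67. The article does not say which SD applies.

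**The case against.** The strongest reply is that 0.43–0.59 describes an analysis the trial does not plan. Missing data will be imputed, mixed models are named, and AUDIT is measured at baseline and at 8 weeks. This stands in part: the range belongs to an unadjusted comparison of observed cases and should carry that label. But imputation creates no information about unmeasured 6-month scores, and the gain from the 8-week score is a few points. Baseline adjustment could do more, yet the article claims no such gain, states no correlation, and reaches 596 with an unadjusted t-test. The article also hopes for relatively low dropout, but its only figures for follow-up are those used here.

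Three stronger readings are tempting and not supported.

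- A reader might call this an arithmetic error. It is not: 596 is right for complete data. The fault is the inconsistency between the sample-size section and the Discussion.
- A reader might infer that d = 0.23 is argued wholly in the wrong direction. One sentence is illogical, since a better-resourced control should narrow the contrast. But the step from 0.20 to 0.23 also rests on minimal guidance and a different comparator. The closest study was unguided, with a booklet in the control arm, and the Background reports larger effects for guided programs. The value may be optimistic, but a coherent reason for it exists.
- A reader might infer that the prize draw, limited to those completing all assessments, removes any incentive at 6 months for those who missed 8 weeks. Under Study design, controls gain the program after the final assessment without mention of the 8-week one; reminders and calls apply to both arms; and no figure shows an effect on retention.

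**Conclusion.** The point holds as an internal contradiction. The 80% applies to 298 analysed per arm, and the article expects 120 to 180. Under that expectation, power at the planned d = 0.23 is about 0.43–0.59 for an unadjusted two-sided t-test on observed cases, with a detectable effect of d = 0.30 to 0.36. It is about 0.45–0.63 with the 8-week AUDIT as auxiliary, and about 0.54–0.71 with baseline adjustment at an assumed correlation of 0.5. On the raw-SD scaling, 0.80 is reached within the expected range only with a baseline correlation of about 0.63–0.65 at 60% follow-up, and higher correlations are needed at lower follow-up.

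All these figures treat loss as equal in the two arms and, for the adjusted versions, rest on correlations that the article does not supply. The shortfall does not depend on questioning 0.23. The illogical sentence about the control condition is a separate, smaller defect.

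**What to change.** Revise Sample size calculation as follows.

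1. State that 80% power at d = 0.23 requires 298 analysed per arm at 6 months.
2. Give power and detectable effect at 40%, 50% and 60% follow-up (0.43, 0.51, 0.59; d = 0.36, 0.32, 0.30). If credit is taken for the 8-week or baseline AUDIT, state the assumed correlation and the SD on which d is scaled.
3. Note that observing 596 at the expected follow-up would need about 994 to 1490 randomised. This is for information and is not a request to enrol more.
4. State that a non-significant primary result will be interpreted through its confidence interval and not as evidence of no effect.
5. Correct the one sentence that infers larger effects from a control with extensive resources, and keep the separate minimal-guidance rationale for 0.23.

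The cost is wording and a less favourable stated power. Recruitment, assessments and participant procedures do not change. The rewording does not raise the power; it makes the stated figure agree with the follow-up the trial expects.

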### Data analysis plan

All analyses will be guided by the intention to treat (ITT) principle. Preliminary testing will assess two things: differences between the two study arms at baseline; and the degree of missing data. Baseline differences will be analysed by (generalised) linear mixed models (LMM). Missing data will be addressed by multiple imputation procedures from Amelia II through R [25]. Imputed data will be analysed with multinomial and binary regression models, considering two-sided tests with a type I error rate of *p* < 0.05 as statistically significant. Results will be cross-checked with complete case analyses of non-imputed data. Besides ITT analyses, we will also perform per-protocol analyses.

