**Methods:**

A two-arm randomized controlled trial (RCT) has been designed to compare the efficacy of a culturally-adapted minimal-guidance online self-help program, the 8-week “Selge” online program against a control condition that consists of a self-administered test of alcohol use and advice regarding usual treatment in Estonia. A target sample of 600 individuals will be recruited and randomly assigned to either condition. The program will contain 10 modules based on principles of cognitive behavioural therapy (CBT) and motivational interviewing (MI). Participants in the control group will have access to the full treatment after they complete their final follow-up assessment. The primary outcome will be change in the Alcohol Use Disorders Identification Test (AUDIT) score between the 6-month follow-up and baseline assessments. Secondary outcomes will include the number of standard drinks consumed and alcohol-free days, drinking motives and motivation for change, as well as changes in mental health. Assessments will be completed at baseline, at the end of treatment, and at 6 months follow-up. Data analysis will follow the intention-to-treat principle and employ (generalised) linear mixed models.

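### The article sets an AUDIT change score as primary outcome, plans baseline tests between randomised arms, and names no adjustment for baseline AUDIT; prespecifying that adjustment would cost nothing and could gain precision

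*Protocol article*

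**What the plan says.** The Primary outcome section states: "The primary outcome will be the change in the Alcohol Use Disorders Identification Test (AUDIT [6]) score between the 6-month follow-up and baseline assessments". The abstract says the same.

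On baseline, the Data analysis plan says: "Preliminary testing will assess two things: differences between the two study arms at baseline; and the degree of missing data". It assigns (generalised) linear mixed models to the baseline comparison. It does not say which variables will be compared or what follows from a significant result.

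On the outcome model, the abstract says: "Data analysis will follow the intention-to-treat principle and employ (generalised) linear mixed models". The Data analysis plan instead says: "Imputed data will be analysed with multinomial and binary regression models, considering two-sided tests with a type I error rate of" 0.05. Neither place lists a covariate, and neither excludes one.

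The design facts that bear on this are:
- simple 1:1 server randomisation, with no stratification mentioned (Randomization and trial flow);
- entry at an AUDIT score of 8 or more (Inclusion and exclusion criteria), with no upper limit (Discussion);
- expected 6-month follow-up of 40–60% (Discussion).

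**The concern.** Two things in the stated text are poorly chosen.

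First, if randomisation works, the null hypothesis of a baseline test is true by design. The test then measures only chance. Because it is called preliminary and has no stated consequence, it also leaves room to choose the adjustment after seeing the result.

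Second, the only role that the article gives baseline AUDIT in the outcome is subtraction. Subtraction fixes the coefficient of baseline at 1. The regression coefficient of 6-month AUDIT on baseline is usually below 1, so the change score over-corrects a chance imbalance: an arm that starts higher by luck tends to look as if it improved more. Simple randomisation and selection on a minimum AUDIT score make both chance imbalance and regression to the mean realistic. Baseline AUDIT is recorded before randomisation, so using it as a covariate needs no new data.

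What is at stake is efficiency and a clean prespecification. The validity of the comparison is not in question.

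**Working it through.** **The plan's own figure.** Inputs from Sample size calculation: d = 0.23, 80% power, α = 0.05; two-sided from the Data analysis plan. A two-sample t test (noncentral t) needs 298 per arm, 596 in total, with power 0.800. This matches the stated figure. The normal approximation gives 297 per arm, and a one-sided test would give 470 in total. The stated N is therefore an unadjusted two-sided comparison.

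**Variance comparison.** Let s be the SD of 6-month AUDIT, k the baseline SD divided by s, and r the baseline to 6-month correlation. Neither k nor r is in the documents; both are assumed below.

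- Change score: variance s²(1 + k² - 2rk)
- Adjusted for baseline: variance s²(1 - r²)
- Difference: s²(k - r)², which is never negative and is zero only when r = k
- Regression slope on baseline: r/k, against the 1 that the change score imposes

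With k = 1 the ratio of adjusted to change-score variance is (1 + r)/2, so the saving is (1 - r)/2.

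| k | r | adjusted / change | variance saved |
|---|---|---|---|
| 1 | 0.4 | 0.84/1.20 = 0.70 | 30% |
| 1 | 0.7 | 0.51/0.60 = 0.85 | 15% |
| 0.8 | 0.4 | 0.84/1.00 = 0.84 | 16% |
| 0.8 | 0.7 | 0.51/0.52 = 0.98 | 2% |
| 0.7 | 0.4 | 0.84/0.93 = 0.90 | 10% |
| 0.7 | 0.7 | 0.51/0.51 = 1.00 | 0% |
| 1.2 | 0.4 | 0.84/1.48 = 0.57 | 43% |
| 1.2 | 0.7 | 0.51/0.76 = 0.67 | 33% |

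At k = 1 the standard error falls by 1 - √0.70 = 16% (r = 0.4) or 1 - √0.85 = 8% (r = 0.7).

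**Power.** The article does not say which SD the d of 0.23 is scaled to. If it is the change-score SD and k = 1, adjustment raises the effective d to 0.23/√0.70 = 0.275 (r = 0.4) or 0.23/√0.85 = 0.249 (r = 0.7). Power at 298 per arm then rises from 0.80 to 0.92 or 0.86. If d is scaled to the raw AUDIT SD instead, still with k = 1, the normal approximation gives 0.727 unadjusted against 0.865 adjusted at r = 0.4, and 0.952 against 0.976 at r = 0.7.

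**The case against.** The strongest reply is that the article is silent on covariates and has not decided against them. Defining an outcome as a change does not fix the model: regressing change on arm and baseline gives the same arm coefficient as regressing the 6-month score on arm and baseline. A covariate list is commonly left to a statistical analysis plan, and none is shown here. The models named are mixed models and multinomial or binary regression, so an unadjusted t test on change is not stated as the outcome analysis. A mixed model with a common baseline mean would recover about the same precision. How the two named sets of models fit together, and how categorical models fit a change in score, is a separate matter.

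This stands against some readings that a reader might infer:

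- *The trial tests baseline instead of adjusting for it.* The text does not say so. It states the tests and is silent on adjustment.
- *A fixed 15–30% of precision is thrown away.* That range is variance, and it needs r of 0.4–0.7 and equal SDs. The entry cut-off may make the baseline SD the smaller one, which shrinks the saving.
- *The planned power is lost without adjustment.* N = 596 reproduces without any adjustment. The effect of 40–60% follow-up is a different issue.
- *Regression to the mean biases the comparison.* Selection at 8 or more applies to both arms alike, and the change-score contrast is unbiased over randomisation.

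The reply does not excuse the baseline tests, which are stated text and not an omission. Nor does it give a reason to leave baseline AUDIT out of the named primary model.

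**Conclusion.** The point holds as a free improvement. The baseline tests are a stated choice that answers no useful question under randomisation. An unadjusted change score would be unbiased but, asymptotically, never more precise than baseline adjustment, and it over-corrects chance imbalance whenever r/k is below 1. That is so for every combination tabulated except k = r = 0.7, where the two methods coincide.

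The size cannot be settled from the documents. Over r = 0.4–0.7 the variance saving runs from 0–10% (SD ratio 0.7), through 2–16% (0.8) and 15–30% (1.0), to 33–43% (1.2). The power gain from 0.80 to 0.86–0.92 at 298 per arm further assumes equal SDs and d on the change-score SD. It would come on top of a calculation that never counted on it.

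**What to change.** In the Data analysis plan, state that the primary analysis is a linear model of 6-month AUDIT on arm, with baseline AUDIT as a prespecified covariate. The alternative is a mixed model over the three assessments with the baseline means constrained equal across arms. Say the same for each secondary outcome that is measured at baseline. Replace the baseline significance tests with a table that describes the arms; reporting the degree of missing data can stay.

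The cost is a sentence or two. No extra data are needed, the treatment contrast is still the between-arm difference in AUDIT change, and the sample size does not have to be revised.

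### The Data analysis plan gives the imputed data to multinomial and binary regression, so it assigns no suitable model to the numeric AUDIT change and contradicts the abstract

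*Protocol article*

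**What the plan says.** Four places in the protocol article bear on the model for the primary outcome.

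- **Primary outcome.** "The primary outcome will be the change in the Alcohol Use Disorders Identification Test" (AUDIT), as a "score between the 6-month follow-up and baseline assessments. The AUDIT is a 10-item self-report measure designed to assess alcohol misuse". This is a difference between two numeric scores.
- **Abstract, Methods.** "Data analysis will follow the intention-to-treat principle and employ (generalised) linear mixed models". The statement is general and is not limited to any one outcome.
- **Sample size calculation.** The trial is sized on a Cohen's d of 0.23, "with 80% power and α = 0.05", which gives 596 in total, 298 per group.
- **Data analysis plan.** Under preliminary testing: "Baseline differences will be analysed by (generalised) linear mixed models (LMM". After the imputation step: "Imputed data will be analysed with multinomial and binary regression models", "considering two-sided tests with a type I error rate of" 0.05. No other outcome model is named in this section.

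**The concern.** Binary and multinomial regression model the probability of falling into a category. They do not estimate a difference in mean change on a score. If the Data analysis plan were applied to AUDIT as it reads, the score would first have to be cut into categories, and the article defines none for the outcome. The quantity estimated would then differ from the stated primary outcome, the cut-point could be chosen after the data are seen, and information would be lost.

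The abstract points to a different family of models. Two analysts, one following the abstract and the other the Data analysis plan, could report different primary results, and each could claim to have followed the protocol.

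The one use that the Data analysis plan makes of mixed models is also hard to explain. A baseline comparison involves a single time point, participants are randomised individually, and no clustering is described.

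**Working it through.** **1. Does the stated sample size identify the test?**

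Inputs, from Sample size calculation and Data analysis plan: d = 0.23 (so SD = 1), α = 0.05 two-sided, power 0.80. Allocation is 1:1 (Randomization and trial flow).

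Normal approximation: n per arm = 2 × ((1.960 + 0.842) / 0.23)² = 296.7, rounded up to 297, or 594 in total.

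Exact two-sample t-test (noncentral t): n per arm = 297.7, rounded up to 298, or 596 in total. Power at 298 per arm is 0.800.

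The exact t-test reproduces the stated 298 and 596. A one-sided t-test would need 235 per arm (470 in total), which does not match. The article names only G*Power and d, so the t-test is inferred, but the match is exact. The trial is sized to compare two means.

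**2. The passages side by side**

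| Place | Outcome or task | Model |
|---|---|---|
| Primary outcome | Numeric change in AUDIT, baseline to 6 months | none named |
| Abstract, Methods | Data analysis in general | (generalised) linear mixed models |
| Sample size calculation | Standardised mean difference, 0.23 | two-sided comparison of means (inferred) |
| Data analysis plan | Baseline differences | (generalised) linear mixed models |
| Data analysis plan | Imputed data, no restriction stated | multinomial and binary regression |

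The first three rows fit together. The last row does not fit them.

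**3. Are outcome categories defined elsewhere?**

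AUDIT thresholds do appear. A score of at least 8 is an entry criterion (Inclusion and exclusion criteria), and the Discussion uses 8 and 20 to describe who may enter the trial. Neither is given as an outcome category or a responder definition.

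**4. Illustration of what dichotomising would cost**

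Assumptions that are not in the documents: AUDIT change is normal, the arms differ by 0.23 SD, and the change is cut so that a proportion p₁ of the control arm falls on the favourable side. Then p₂ = Φ(Φ⁻¹(p₁) + 0.23).

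Power = Φ[(|p₂ − p₁| − 1.960 × s₀) / s₁], where p̄ = (p₁ + p₂)/2, s₀ = √(2p̄(1 − p̄)/n) and s₁ = √((p₁(1 − p₁) + p₂(1 − p₂))/n).

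Example with p₁ = 0.50 and n = 298: p₂ = 0.591, s₀ = 0.0408, s₁ = 0.0406. Power = Φ[(0.0910 − 0.0799) / 0.0406] = Φ(0.27) = 0.61.

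| Control proportion p₁ | p₂ | Power at 298 per arm | Total N for 80% power |
|---|---|---|---|
| 0.20 | 0.270 | 0.53 | 1138 |
| 0.30 | 0.384 | 0.58 | 994 |
| 0.50 | 0.591 | 0.61 | 940 |
| 0.70 | 0.775 | 0.54 | 1088 |
| 0.80 | 0.858 | 0.47 | 1318 |

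The t-test comparator at 298 per arm is 0.80. The table is not symmetric about 0.50, so the direction of the cut matters as well as its position.

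**5. The same comparison on completers only**

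The Discussion expects 40–60% follow-up at 6 months. With 600 recruited, that is 600 × 0.60 / 2 = 180 or 600 × 0.40 / 2 = 120 per arm.

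| Completers per arm | t-test | Median split | Loss from dichotomising |
|---|---|---|---|
| 180 | 0.59 | 0.41 | about 0.18 |
| 120 | 0.43 | 0.29–0.30 | about 0.13 |

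The range in the last row reflects pooled against unpooled variance in the two-proportion formula. The fall from 0.80 to 0.59 or 0.43 is due to attrition and is a separate matter. These figures also describe completers, whereas the disputed sentence concerns imputed data.

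**The case against.** **The abstract does name a suitable model.** This stands. A linear mixed model can estimate a difference in AUDIT change, so it would be wrong to say that the article as a whole offers nothing suitable. The fault is narrower: the section that governs the analysis does not apply that model to the outcomes and names others instead.

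**The categorical regressions may be meant for categorical secondary variables.** Use of professional help is one such variable, and the Data analysis plan never says that AUDIT itself goes into these models. A reader might infer that the plan forces AUDIT into categories; the text does not go that far. But it refers to the imputed data without restriction and gives no other outcome model, and most of the listed outcomes are numeric (drinks, alcohol-free days, motive scores, 0–10 ratings, MHI-5).

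**Generalised mixed models include logistic forms.** True, but that supplies no analysis of the numeric primary outcome, and the regressions in the Data analysis plan are not described as mixed.

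**The details belong in a statistical analysis plan.** That would answer an omission. Here the article states a model, and it does not fit the stated outcome.

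**The two methods may simply have been swapped.** A reader might infer this from the odd use of mixed models at baseline. It is possible, but text lost in condensing the article would explain it equally well, and nothing in the document decides between them.

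**Conclusion.** The point holds as an inconsistency in the stated analysis. The Data analysis plan assigns no suitable model to the numeric primary outcome, contradicts the abstract, and does not match the comparison of means for which 596 was calculated. This conclusion rests on the text and the exact reproduction of N, and on no assumption about power. It should be corrected because it concerns the main test of the trial.

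The power figures only illustrate the stakes. They assume normality, a 0.23 SD shift and cut-points that the documents do not contain, and no multinomial model was computed. On those terms, dichotomising would take power at 298 per arm from 0.80 to about 0.47–0.61. A reader might set the completer figures of 0.41 and about 0.30 against the planned 0.80 and blame the whole gap on the model. That would be wrong, because the like-for-like comparators are 0.59 and 0.43.

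The stated N is not in error for its own inputs.

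**What to change.** Reconcile the abstract and the Data analysis plan by naming one primary analysis of AUDIT change at 6 months as a continuous outcome. One acceptable form: in each imputed data set, fit a linear mixed model with arm, time and arm-by-time, and pool the arm difference at T2 by Rubin's rules. A linear model adjusted for baseline AUDIT would also fit the stated outcome. Either will serve, but the text should commit to one.

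Limit binary and multinomial regression to categorical variables, such as whether professional help was used, and remove mixed models from the baseline comparison.

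The cost is about two sentences in the Data analysis plan. No new data are needed, and the calculation behind N = 596 is unchanged.
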